## Abstract

**Background:**

Perioperative care in colorectal surgery is systematically defined in the Enhanced Recovery After Surgery (ERAS) protocol. The ERAS protocol improves perioperative care in a multimodal way to enhance early and safe release from the hospital. Adequate compliance to the elements of the ERAS protocol is multifactorial. There are still opportunities to improve compliance of the protocol by actively involving the patient. The main objective of this study is to investigate whether compliance of selected items in the ERAS protocol can be improved through actively involving patients in the ERAS care pathway through the use of a patient-centred mobile application.

**Methods:**

A multicentre randomized controlled trial will be conducted. Patients undergoing elective colorectal surgery, who are 18 years or older and in possession of an eligible smartphone, will be included. Patients assigned to the intervention group will install a patient-centred mobile application to be guided through the ERAS care pathway. Patients in the control group will receive care as usual. Both groups will wear an activity tracker. The primary outcome is overall compliance to selected active elements of the ERAS protocol, as registered by the patient. Secondary outcomes include Patient Reported Outcome Measures (PROMs) such as health-related quality of life, physical activity, and patient satisfaction of received care. Care-related outcomes, such as length of hospital stay, number of complications, re-intervention, and readmission rates, will also be assessed.

**Results:**

The enrolment of patients will start in the second quarter of 2019. Data collection had not begun by the time this protocol was submitted.

**Conclusion:**

We hypothesize that by providing patients with a patient-centred mobile application, compliance to the active elements of ERAS protocol can be improved, resulting in an increased health-related quality of life, physical activity, and patient satisfaction.

**Trial registration:**

Netherlands Trial Register, NTR7314, prospectively registered on the 9th of November 2017 (http://www.trialregister.nl).

**Electronic supplementary material:**

The online version of this article (10.1186/s12893-019-0588-3) contains supplementary material, which is available to authorized users.

## Background

The Enhanced Recovery After Surgery (ERAS) Society was formed in 2001 by a group of European surgeons to optimize clinical outcomes of patients undergoing surgery. Initially the ERAS Study Group published a consensus document with a scientific, evidence-based approach about the perioperative care for colonic resections (2005) and colorectal surgery (2009) [1]. Compared to routine care in elective colonic surgery, application of the ERAS protocol proved to reduce surgical stress, resulting in a better postoperative physiological status of the patient and improved mobilization short-term after surgery [2–6]. These outcomes contribute to faster postoperative recovery, shorter length of stay in hospital (LOS), and reduced rates of morbidity [7–9]. Nowadays, the ERAS protocol consists of 24 core elements (Table 1), and in order to successfully implement these 24 elements, a multidisciplinary team of anaesthetists, surgeons, nurses, physiotherapist and dieticians is essential. Local ERAS protocols, based on the ERAS guideline, can vary depending to the performing medical centre. The ERAS protocol elements are divided into preadmission, preoperative, intraoperative and postoperative phases, which, in their synergy, improve recovery after surgery [10]. An element is considered ‘active’ when some or full contribution of the patient is required. Elements are ‘passive’ when they do not directly depend on or require patient’s actions (Table 1) [11].

**Table 1 Tab1:** ERAS society guideline elements for colonic resections

Element	Responsible professional	Involvement patient
Preadmission		
1 Cessation of smoking and excessive intake of alcohol	Surgeon, patient	Active
2 Preoperative nutritional screening and, as needed, assessment and nutritional support	Surgeon	Active/Passive
3 Medical optimization of chronic disease	Anaesthetist	Passive
Preoperative		
1 Structured preoperative information and engagement of the patient and relatives or caretakers	Nurse	Passive
2 Preoperative carbohydrate treatment	Nurse	Active/Passive
3 Preoperative prophylaxis against thrombosis	Surgeon	Active/Passive
4 Preoperative prophylaxis against infection	Anaesthetist	Passive
5 Prophylaxis against nausea and vomiting	Anaesthetist	Passive
Intraoperative		
1 Minimal invasive surgical techniques	Surgery	Passive
2 Standardized anesthesia, avoiding long-acting opioids	Anaesthetist	Passive
3 Maintaining fluid balance to avoid over- or under hydration, administer vasopressors to support blood pressure control	Anaesthetist	Passive
4 Epidural anesthesia for open surgery	Anaesthetist	Passive
5 Restrictive use of surgical site drains	Surgeon	Passive
6 Removal of nasogastric tubes before reversal of anesthesia	Anaesthetist	Passive
7 Control of body temperature using warm air flow blankets and warmed intravenous infusions	Anaesthetist	Passive
Postoperative		
1 Early mobilization (day of surgery)	Patient	Active
2 Early intake of oral fluids and solids (offered the day of surgery)	Patient	Active
3 Early removal of urinary catheters and intravenous fluids (morning after surgery)	Nurse	Active/Passive
4 Use of chewing gums and laxatives and peripheral opioid-blocking agents (when using opioids)	Patient	Active
5 Intake of protein and energy-rich nutritional supplements	Patient	Active
6 Multimodal approach to opioid-sparing pain control	Anaesthetist	Passive
7 Multimodal approach to control of nausea and vomiting	Anaesthetist	Passive
8 Prepare for early discharge	Nurse, patient	Active/Passive
9 Audit of outcomes and process in a multi-professional, multidisciplinary team on a regular basis	Whole team	Passive

In addition to regular use of the protocol, the ERAS Society recommends conducting a systematic audit to gather insights into clinical- and care-related outcomes, such as LOS, readmission, and postoperative complications, and to measure protocol compliance [9]. Studies investigating ERAS protocol compliance demonstrate that higher compliance rates are significantly associated with improved clinical outcomes such as shorter LOS, fewer postoperative complications, reduced 30-day morbidity, and reduced readmission rates [12–15]. Messenger et al. analysed the protocol compliance of 21 individual ERAS elements in a systematic review. The pooled results of 12 studies showed a 69, 72, and 53% adherence to the protocol within the pre-, peri- and postoperative phases [16]. ERAS protocol deviation is considered to be most critical in the postoperative phase, when mobilization and resumption of oral intake should be stimulated in order to not delay hospital discharge and to minimize postoperative complications. Improving postoperative protocol compliance is challenging but there is certainly room for improvement [17], especially since the majority of the postoperative elements are considered ‘active’ and, therefore, depend on patients’ actions directly.

With regards to improving patient participation in the ERAS care pathway, innovative technologies, such as mobile applications and wireless monitoring, could have great potential [18, 19]. Use of these eHealth solutions by patients can be educational, engaging, and stimulating. It might also enhance empowerment and let patients feel more in control of their own health [20]. Cook et al. used a wireless accelerometer to monitor patients postoperatively and demonstrated a significant relationship between the number of steps taken in the early recovery period and LOS in an older cardiac surgery population [21]. A small study of Mundi et al. showed that using a smartphone application for education and engagement of patients prior to bariatric surgery could be beneficial [22].

By conducting this randomized controlled trial (RCT) we want to investigate whether a patient-centred mobile application can significantly improve compliance to the active elements of the ERAS protocol significantly by patients undergoing colorectal surgery.

## Methods

### Study setting

The ERAS APPtimize study is a multicentre RCT that will be conducted in the Amsterdam University Medical Centres (UMCs), locations AMC and VUMC, in the Netherlands. APPtimize is a blended word, combining ‘APP’ and ‘timize’ from ‘application’ and ‘optimization’. The SPIRIT (Standard Protocol Items: Recommendations for Interventional Trials) 2013 statement will be followed and the trial will be reported in accordance to the CONSORT-EHEALTH(Consolidated Standards of Reporting Trials of Electronic and Mobile Health Applications and online TeleHealth) checklist V1.6.2. A completed informed consent form is required to participate in this study. The ERAS APPtimize study will be conducted in line with the declaration of Helsinki. Approval of the local medical ethics committee for this study was obtained (registration number NL63874.018.17) and the study is registered at the Netherlands Trial Registry (NTR7314).

### Study population

The study population consists of patients scheduled to undergo colorectal surgery for either benign or malignant conditions. Patients must be 18 years or older and in possession of a smartphone operating iOS 9 (release date: September 16, 2015) and up or android 8.0 (release date: August 21, 2017) and up. Participants who meet one or more of the following criteria will not be considered for inclusion:

Exclusion criteria:
Palliative surgery or surgery following neo-adjuvant radio- or chemotherapyElective surgery for previously established complications (e.g. enteral fistula, presacral abscess) with the exception of colostomy correctionPatients with a Karnofsky score ≤ 40Incompetence of understanding the Dutch languageVisual impairment, unless well corrected with visual aidsPhysical or mental disabilities limiting the use of a mobile applicationWhen pre-operatively is estimated by the treating surgeon that adherence to the ERAS protocol postoperative is not feasibleIf expected LOS is 3 days or less after surgeryMultiple organ resection

### Investigational intervention

#### Content development

A consensus meeting was organized with a multidisciplinary team of caregivers, representing both Amsterdam UMCs’ locations. Both locations practice almost all the elements from the 2012 ERAS society recommendations for colorectal surgery as part of their ‘care as usual’ except for ‘nutritional screening’ and ‘chewing gum as a laxative’. [9] Active ERAS elements, elements that depend on patient involvement, were included in the application. The multidisciplinary team of caregivers evaluated the ERAS elements for their eligibility to be included in the application. Although ‘nutritional screening’ was not part of current ‘care as usual’, the multidisciplinary team thought it would be useful to include this element in the application. Table 2 displays all elements that were included in the application. In ‘Additional file 1’, one can find the functional design of the application. The functional design illustrates the workflow through the application and the basic layout. After the first version of the application will be developed, ‘patient experts’ will be invited to test the application and review the content of the application.

**Table 2 Tab2:** ERAS elements in the APPtimize application

Preadmission	
1. Cessation of smoking and excessive intake of alcohol	
2. Preoperative nutritional screening and, as needed, assessment and nutritional support	
Preoperative	
3. Preoperative carbohydrate treatment	
4. Preoperative prophylaxis against thrombosis	
Postoperative	
5. Early mobilization (day of surgery)	
6. Early intake of oral fluids and solids (offered the day of surgery)	
7. Early removal of urinary catheters and intravenous fluids (morning after surgery)	
8. Use of laxatives	
9. Intake of protein and energy-rich nutritional supplements	
10. Prepare for early discharge	

#### Technological development

The application is developed by a third party. The application will work on smartphones operating iOS 9 (release date: September 16, 2015) and up or android 8.0 (release date: August 21, 2017) and up. Applications for smartphone destined for diagnosis, prevention, monitoring, or relieve of diseases are considered medical devices [23]. The application used in the APPtimize study is developed specifically for patients having to undergo colorectal surgery and is therefore considered a medical device. Therefore, the application is submitted for CE-marking.

#### Activity tracker

We chose to use an activity tracker from the company Fitbit because it is deemed to provide the best accuracy results, as reflected upon in available literature [24, 25]. The selected Fitbit type is the Flex 2, which does not have a visual display on the bracelet. The intervention group receives feedback about their activity through the APPtimize application but the control group should not receive any feedback about their activity. Therefore, using an activity tracker without a visual display, is, to our belief, the most appropriate way to minimize information bias. The activity tracker will monitor physical activity, measured in steps per day, in both groups. Other information that is captured with the Flex 2 is not represented in the ERAS APPtimize application. Participants of both study groups have to wear the tracker continuously, from 7 days prior to surgery until 21 days after surgery. The battery of the activity tracker will last about 5 days, therefore patients will be instructed to charge their activity tracker during the night. As for the intervention group, the activity data will be stored in the database automatically via the mobile application. The participants in the control group are instructed to send the activity tracker to the coordinating researcher after the 4 weeks of use. The corresponding researcher will process the activity data of the control group to the database manually through the Fitbit application.

#### Usability testing

The usability of the app will be tested by a group of ‘patient experts’. Members of different patient associations with expertise in colorectal diseases and surgery were approached to test the application. Through multiple cognitive walkthrough sessions, the weaknesses of the application will be determined and adjustments can be made. Furthermore, the use of the applications will continuously be monitored in order to improve the application during and after completion of this trial.

### Control and intervention group

#### APPtimize study group

Patients in the intervention group will receive instructions how to download the APPtimize application shortly after the operation is scheduled. The application will be used until 42 days postoperative. The selected ERAS elements (Table 2) have been translated into practical patient-tailored features that can be viewed in the application any time but will also be brought to the patient’s attention through push notifications (Table 3) at set times. The push notifications attempt to prompt the patient to undertake action towards an ERAS element that requires action at that specific moment. The main goals of the application are: to inform and educate the patient, to stimulate patient participation throughout the perioperative care pathway, and to monitor daily activity. All information provided by the application can be accessed at any moment but also once an ERAS element of the care pathway is considered completed. Figure 1 illustrates the layout of the application, with the third screenshot showing the application’s feature ‘dashboard’. This feature represents the completion of three subjects: 1. completion of the daily set activity goal 2. completion of the active ERAS elements, and 3. completion of self-registered questionnaires throughout the entire study.

**Table 3 Tab3:** Push notifications

Preoperative day	Notification
−21	Information about nutrition
−20	Information about smoking
−16	Information about preparation before surgery
−8	Instructions to wear the activity tracker
−2	No alcohol 24 h before surgery
−1	Instructions to drink the pre-operative nutrition drink (4x)
0	Instructions to drink the pre-operative nutrition drink (1x)
Postoperative day	Notification
0	Instructions to wear the activity tracker
1,2,3,..,day of discharge	information of daily goals
1,2,3,..,day of discharge	Information on progress of daily activity
1,2,3,..,day of discharge	Check progress to discharge in the overview of ‘completion of goals’

**Fig. 1 Fig1:**
[figure not shown]
Screenshots APPtimize mobile application. NB Written permission to publish content relating to the APPtimize mobile application was obtained from the designer

To measure daily activity, the patient will be instructed to continuously wear the activity tracker, starting 7 days prior to hospital admission or as soon as possible after surgery is scheduled if this period is less than 7 days. The mean daily step count during this preoperative period will be used as a baseline reference value that will be used to calculate the individual postoperative daily step count goal. The postoperative daily step count goal is based on a daily increasing percentage of the mean preoperative daily step count (Table 4). The percentages are comparable to the usual activity instructions given by the local physiotherapist and generally recommended in literature [26]. Patients will receive instructions to wear the activity tracker until 21 days postoperative, since the biggest increase in activity is expected during this period [27].

**Table 4 Tab4:** Daily step goal

	Days	Registration
Preadmission	7	Daily step count^a^
	Days	Daily step goal
Postoperative	0	50
	1	2,0% * preadmission step mean^b^
	2	6,7% * preadmission step mean^b^
	3–5	19,6% * preadmission step mean^b^
	6–8	28,9% * preadmission step mean^b^
	9–11	38,3% * preadmission step mean^b^
	12–14	47,7% * preadmission step mean^b^
	15–17	57,0% * preadmission step mean^b^
	18–20	66,5% * preadmission step mean^b^
	21	76,0% * preadmission step mean^b^

^a^days are valid measurements when activity tracker is worn ≥10 h

^b^Daily step mean = (Steps/day preadmission)/number of measured days

#### Control group

The control group will receive ‘care as usual’. However, to accurately compare pre- and postoperative activity between both groups, the control group will be instructed to also wear an activity tracker 7 days prior to hospital admission or as soon as possible after surgery is scheduled if this period is less than 7 days. The activity tracker will have to be worn until 21 days after surgery. No feedback is provided through the activity tracker to the control group patient, as it might influence the daily activity. To register the completion of the ERAS elements of the past day, patients of the control group will be instructed to fill out a checklist of completion of the ERAS elements in a diary once a day.

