### Outcomes

The primary outcome is the overall average compliance to the selected active ERAS elements (Table 2). Since the application is patient-centred and focusses on empowering patients to get in control of their own health, the PROMs, such as health related quality of life and patient satisfaction, are considered important secondary outcome parameters. Other secondary outcomes include postoperative outcome parameters (e.g. complications), gastro-intestinal recovery (e.g. time to passage of stool), activity and pain measurements. Table 5 describes all study outcomes and how and when these will be measured.

**Table 5 Tab5:** Time points and measurements

Enrolment		T0	T1	T2	T3	T4	T5	T6	T7	Registered in/with:
	Eligibility screen	x								
	Informed consent	x								
	Allocation	x								
Interventions		T0	T1	T2	T3	T4	T5	T6	T7	
Intervention group	Download mobile application	x								
	Wear activity tracker		O	O	O	O	O	O		
Control group	Wear activity tracker		O	O	O	O	O	O		
Data measurements		T0	T1	T2	T3	T4	T5	T6	T7	
Baseline characteristics	General characteristics	x								Sex, age, ASA, BMI, smoking, alcohol intake
	Disease related characteristics	x								Disease, operation
	eHealth literacy assessment	x								eHEALS
Protocol compliance *(as reported by patients)*	1. Cessation of smoking and excessive intake of alcohol	x								Y/N questions in app or with paper form
	2. Preoperative nutritional screening and, as needed, assessment and nutritional support	x								Y/N questions in app or with paper form
	3. Preoperative carbohydrate treatment			x						Y/N questions in app or with paper form
	4. Preoperative prophylaxis against thrombosis			x						Y/N questions in app or with paper form
	5. Early mobilization (day of surgery)				O	O				Y/N questions in app or with paper form
	6. Early intake of oral fluids and solids (offered the day of surgery)				O	O				Y/N questions in app or with paper form
	7. Early removal of urinary catheters and intravenous fluids (morning after surgery)					O				Y/N questions in app or with paper form
	8. Use of laxatives					O				Y/N questions in app or with paper form
	9. Intake of protein and energy-rich nutritional supplements					O				Y/N questions in app or with paper form
	10. Prepare for early discharge					O				Y/N questions in app or with paper form
Postoperative data ≤30 days *(retrospective collection)*	Length of hospital stay								x	EHR
	Overall morbidity ≤30 days								x	EHR

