### Group allocation and blinding

After inclusion, participants are randomly assigned to the mobile application (intervention) group or standard care (control) group in a 1:1 ratio, using an internet randomization module with stratification for benign or malignant pathology and age (> 50 years and < 50 years). Random block sizes of 2, 4, and 6 will be used. The coordinating researcher will initiate the allocation sequence and following study enrolment.

Participants, professionals of the healthcare team, and outcome assessors will not be blinded to the treatment allocation. Patients will be instructed to not tell other patients in their ward if they were assigned to the intervention or control group.

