### Data collection

Data from the intervention group will mostly be automatically collected and stored in the database. For instance, results from the self-reported questionnaires will be sent from the application to the database. Some data will be collected through the Electronic Health Record (EHR) by the coordinating researcher and entered in case report forms (CRFs). As for the control group, the data from the patient dairy, the self-registered questionnaires, and data from the activity tracker will be manually entered in the CRF. Trial findings will be stored in accordance with local data protection laws and handled in confidence. A data protection impact assessment has been part of the protocol.

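### The unblinded, self-reported primary outcome is captured by the app in one arm and a paper diary in the other, with no second source, so a recording difference in either direction could mimic or hide a compliance difference

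*Protocol article*

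**What the plan says.** The Abstract (Methods) defines the endpoint: "The primary outcome is overall compliance to selected active elements of the ERAS protocol, as registered by the patient". Table 5 (Outcomes) lists ten elements and gives each the same source, "Y/N questions in app or with paper form". Under Group allocation and blinding: "Participants, professionals of the healthcare team, and outcome assessors will not be blinded to the treatment allocation".

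The route differs by arm:

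- **Intervention.** The app collects the answers and is also the treatment. Under APPtimize study group: "The push notifications attempt to prompt the patient to undertake action towards an ERAS element that requires action at that specific moment". Its dashboard shows the patient, besides the daily activity goal, "completion of the active ERAS elements, and 3. completion of self-registered questionnaires throughout the entire study". Under Data collection: "Data from the intervention group will mostly be automatically collected and stored in the database".
- **Control.** Patients "will be instructed to fill out a checklist of completion of the ERAS elements in a diary once a day" (Control group), covering the past day. Data collection says that the diary is entered by hand.

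Other sources exist in both arms. Under Activity tracker: "The activity tracker will monitor physical activity, measured in steps per day, in both groups". The coordinating researcher extracts data from the electronic health record (EHR) and screens each participant's record after follow-up (Data collection; Potential confounders). Table 5 uses the EHR for outcomes such as length of stay and readmission, and the tracker for steps. It assigns neither to a compliance element.

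**The concern.** In one arm the measuring instrument is part of the treatment; in the other it is a paper form. Neither patients nor staff are blinded, and Table 5 gives no second source against which the answers could be checked. If patients tick, skip or misjudge elements differently in the app and on paper, that difference enters the primary comparison in full.

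The protocol guards against this kind of bias elsewhere. Under Activity tracker it chooses a device without a display so as to limit information bias in the step counts. The primary outcome gets no comparable protection. The Discussion considers only one mechanism, that diary and tracker may activate controls and shrink the difference, and argues that a significant result would then be all the more relevant. That argument does not hold if the arms record differently, because part or all of a significant difference could then come from recording.

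**Working it through.** **Inputs** (Sample size calculation): compliance 57% versus 62%, so an effect of 5 points; SD 9; two-sided alpha 0.05; power 90%; 70 per group; 10% loss to follow-up. The recording differences below are assumptions, since the document gives none.

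**1. The protocol's own figure.** Normal approximation: n = 2 × 9² × (1.960 + 1.282)² / 5² = 68.1, so 69 per arm. The two-sample t-test gives 69.06, rounded up to 70. Total: 140 / 0.9 = 155.6, so 156. Both stated figures reproduce, and power at 70 per arm is 0.91. The sample size arithmetic is not at fault.

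**2. How small the effect is.** On an average of ten yes/no elements, 5 points is 0.05 × 10 = half an element per patient.

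**3. Precision.** SE = 9 × √(2/70) = 1.52 points. The smallest significant observed difference is 1.96 × 1.52 = 2.98, about 3 points.

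**4. No true effect, recording difference of b points.** P(significant) = 1 − Φ(1.96 − b/SE) + Φ(−1.96 − b/SE).

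- b = 0: 0.05 (nominal)
- b = 1: 0.101
- b = 2: 0.260
- b = 3: 0.505
- b = 5: 0.908

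**5. Opposite direction.** With a true effect of 5 points and 2 points of under-recording in the app arm, the expected observed difference is 5 − 2 = 3 points. Power falls from 0.91 to 0.505. With 1 point it is 0.75, with 3 points 0.26.

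**The case against.** A reader might infer that the design biases the result in favour of the app. For example, if controls leave 10% of completed elements unticked, a 57% score falls by 0.10 × 57 = 5.7 points, more than the whole planned effect. The documents do not support this reading:

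- **Direction.** Nothing shows that paper under-records or that the app over-records. App users may skip entries, and a daily diary may be filled in completely.
- **Scoring of blanks.** The 5.7 points require blanks to count as not completed, in one arm only. Both arms answer yes/no items, so a blank can be told from a no. Data analyses allows imputation where applicable, and its example of a non-completed element is a catheter that could not be removed on time, not an unanswered item. The 57% is also an average of two elements, not of ten.
- **Prompts.** The notifications in Table 3 inform, instruct or report progress; none asks the patient to record an element. Extra action that they cause is treatment effect, not bias. The app's workflow is in an additional file that is not shown, so it is not known when app users answer or what is on screen when they do.
- **EHR coverage.** The article does not say that laxatives, supplements or thromboprophylaxis are charted reliably enough to replace self-report.
- **Other sources differ by arm too.** Tracker data arrive automatically through the app in one arm and by returned device in the other. The reminder on the day of surgery to wear the tracker reaches app users only. EHR extraction would be unblinded.

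These points stand. They remove the claim of a known direction, the 5.7-point figure, and the case for re-sourcing most elements. They do not remove the core: medium and feedback differ by arm in an unblinded self-report, and Table 5 names no other source for it.

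**Conclusion.** The concern holds in a limited form. The way the primary outcome is captured differs by arm and is not checked against another source, so a recording difference could be read as a compliance difference or could hide one. The size and direction of any such difference cannot be known from the document.

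The planned effect makes this matter. A recording difference of about 3 points would give a significant result about half the time with no true effect, and 2 points against the app would reduce power to about one half. These figures rest on the protocol's SD of 9, on 70 analysed patients per arm, on a normal approximation and on assumed recording differences. They measure vulnerability and do not estimate bias. Blinding is not feasible here, but the difference in instruments can be reduced and part of the outcome can be verified.

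**What to change.** - **Same questions.** Use identically worded yes/no items with the same recall period in both arms. Treat a blank as missing, not as not completed, by the same rule in both arms.
- **EHR.** During the record review already planned, extract catheter and infusion removal (element 7), and any other element found to be reliably charted, by one rule in both arms.
- **Tracker.** Derive early mobilization (element 5) from steps, with one criterion and one wear-validity rule for both arms, fixed by the trial team in advance. Table 4 gives a wear rule for preadmission days only.
- **Analysis.** Prespecify a key sensitivity analysis of the primary outcome in which these elements replace self-report, and report agreement between sources by arm. Do not attribute a significant result to better compliance, as the Discussion foresees, unless this analysis supports it.

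The check is partial. If a recording difference were spread evenly over ten elements, replacing two would remove only 2/10 of it. The agreement by arm is therefore as informative as the change in the score.

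The cost is a few extra CRF fields, a stated fallback to patient report where charting or tracker wear is insufficient, and an EHR extractor who is not blinded. The self-reported score can remain primary. Sending controls timed smartphone forms is not required, since it could add to the activation of controls that the Discussion already expects.
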